## Abstract

**Background:**

Atraumatic lower limb amputation is a life-changing event for approximately 185,000 persons in the United States each year. A unilateral amputation is associated with rapid changes to the musculoskeletal system including leg and back muscle atrophy, strength loss, gait asymmetries, differential mechanical joint loading and leg length discrepancies. Even with high-quality medical care and prostheses, amputees still develop secondary musculoskeletal conditions such as chronic low back pain (LBP). Resistance training interventions that focus on core stabilization, lumbar strength and dynamic stability during loading have strong potential to reduce LBP and address amputation-related changes to the musculoskeletal system. Home-based resistance exercise programs may be attractive to patients to minimize travel and financial burdens.

**Methods/design:**

This study will be a single-assessor-blinded, pre-post-test randomised controlled trial involving 40 men and women aged 18–60 years with traumatic, unilateral transtibial amputation. Participants will be randomised to a home-based, resistance exercise group (HBRX) or a wait-list control group (CON). The HBRX will consist of 12 weeks of elastic resistance band and bodyweight training to improve core and lumbopelvic strength. Participants will be monitored via Skype or Facetime on a weekly basis. The primary outcome will be pain severity (11-point Numerical Pain Rating Scale; NRS_pain_). Secondary outcomes will include pain impact on quality of life (Medical Outcomes Short Form 36, Oswestry Disability Index and Roland Morris Disability Questionnaire), kinematics and kinetics of walking gait on an instrumented treadmill, muscle morphology (muscle thickness of multifidus, transversus abdominis, internal oblique), maximal muscle strength of key lumbar and core muscles, and daily step count.

**Discussion:**

The study findings will determine whether a HBRX program can decrease pain severity and positively impact several physiological and mechanical factors that contribute to back pain in unilateral transtibial amputees with chronic LBP. We will determine the relative contribution of the exercise-induced changes in these factors on pain responsiveness in this population.

**Trial registration:**

ClinicalTrials.gov, ID: NCT03300375. Registered on 2 October 2017.

**Electronic supplementary material:**

The online version of this article (doi:10.1186/s13063-017-2362-0) contains supplementary material, which is available to authorized users.

## Background

Amputation to the lower extremity is a life-changing event. Approximately two million Americans live with limb loss. An estimated 45% of these amputations are caused by traumatic mechanisms [1, 2]. Once the injury has healed and a prosthetic limb is fitted, the long-term care focuses on maintenance of the prosthesis fit and optimizing physical function [3]. However, even with the use of high-quality prostheses, biomechanical symmetry of gait remains permanently altered [4]. A unilateral transtibial amputation leads to progressive skeletal muscle atrophy in the affected lower extremity [5] and back [6]. The collective effects of asymmetric gait, loss of muscle mass, and reduction of strength increase mechanical stresses at the lumbar spine [4, 7]. These stresses contribute to low back pain (LBP) onset. LBP is a secondary complication in over half of the unilateral amputee population [8–10]. LBP interferes with physical and mental well-being and overall quality of life (QOL) [10].

Long-term care for amputees requires a team of physicians, prostheticians, therapists, and other specialists. Patients often travel long distances to receive their care, and many have resource limitations. Patients may not be able to maintain consistent long-term relationships with therapists or purchase fitness memberships due to financial constraints. Effective home-based interventions that target LBP could minimize travel or cost burden to the patient and substantially impact the secondary disease burden. An exercise mode with strong potential for a home-based intervention is resistance exercise. In the general population, resistance exercise is associated with lower odds of developing LBP [11]. Resistance exercise increases lumbar muscle strength, physical functional, and both physical and mental aspects of QOL [12–17]. The impact and effectiveness of resistance training on chronic LBP severity and pain impact in amputees is not yet known. Moreover, the mechanisms that may contribute to the effectiveness of strength training on LBP relief in amputees are not clear. These evidence gaps are significant barriers to the optimization of care for this special population.

The aims of this study are to determine whether home-based resistance exercise (HBRX) among unilateral transtibial amputees with LBP can reduce LBP severity and its impact on QOL and improve the biomechanical symmetry of gait. The relative contribution of key factors that predict pain responsiveness with HBRX will be determined. The research hypotheses are as follows: (1) HBRX will reduce subjective pain ratings, pain medication use, and the impact of pain on QOL; (2) HBRX will reduce gait asymmetries and increase gait velocity; and (3) HBRX-induced changes in lumbar muscle strength, lumbar muscle cross-sectional area, and perceived QOL will predict pain responsiveness for LBP in unilateral transtibial amputees.

## Methods

### Trial design

This study will be a single-assessor-blinded, pre-post-test randomised controlled trial. The study will follow the principles of the Consolidated Standards of Reporting Trials for randomized, two-group, parallel studies [18, 19]. Figure 1 provides the study flow and Fig. 2 shows a version of the Standard Protocol Items: Recommendations for Interventional Trials (SPIRIT) Figure for the trial. Details of study methodology are outlined in Additional file 1, SPIRIT Checklist. There will be an HBRX intervention group and a wait-list control group (CON). Outcome measurements will be performed before the intervention period (baseline assessment) and immediately after the 12-week intervention (post-testing assessment). Baseline and follow-up measurements will be evaluated blindly.

**Fig. 1 Fig1:**
[figure not shown]
Study flow diagram

**Fig. 2 Fig2:**
[figure not shown]
Schedule of enrollment, interventions, and assessments

### Ethical aspects

This study and its procedures were approved by the University of Florida Institutional Review Board (UF IRB) (protocol number 201701256). Although unanticipated, any changes to the protocol and study procedures will be requested through UF IRB and subsequently to ClinicalTrials.gov and the study sponsor. Written informed consent will be obtained from all candidates who agree to participate and meet all the inclusion/exclusion criteria. Data will be used only in aggregate and no identifying characteristics of individuals will be published or presented. Confidentiality of data will be maintained by using research identification (ID) numbers that uniquely identify each individual. Safeguards will be established to ensure the security and privacy of participants’ study records. Appropriate measures will be taken to prevent unauthorized use of study information. Data other than demographic information do not use names as an identifier. The research ID number will be used. The research records will be kept in a locked room on site. The files matching participants’ names and demographic information with research ID numbers will be kept in a separate room and will be stored in a locked file that uses a different key from that of all other files. Only the study team members will have access to these files, and they will be asked to sign a document that they agree to maintain the confidentiality of the information. Only the study team members and the UF IRB will have access to the full data set.

### Study population

A total of 40 transtibial amputees aged between 18 and 65 years will be recruited for this study. Participants will be recruited from a major regional prosthetics center and from the greater north Florida community via relationships with local prosthetic clinics and amputee support groups. Study flyers, social media posts, and online web advertisements will also be used. Participants will be eligible if they meet the following inclusion and exclusion criteria. Inclusion criteria: men or women aged 18–60 years, traumatic transtibial amputation more than 1 year prior to enrollment, current prosthesis worn for at least 6 months, suffering from chronic LBP (>3 months with at least three pain episodes per week), must have regular access to a computer for Skype®, or a mobile phone or iPAD to perform Facetime; prosthesis K-level of K2 or greater (indicating the subject is able to ambulate and traverse low-level environmental barriers such as curbs, stairs, or uneven surfaces) [20]. Exclusion criteria: dysvascular amputation, acute back injury, pregnancy, any other chronic back pathology (i.e., herniated disc, ankylosing spondylosis, other related neurological disease), pain symptoms or functional limitations (including those that may require assistive devices) that preclude participation in resistance exercise or physical activity, back surgery within the past 2 years that restricts daily physical activities, and currently enrolled in any other resistance or strengthening exercise interventions. Written informed consent will be obtained from each participant.

The primary outcome of the study is the Numerical Pain Rating Scale (NRS_pain_) value for LBP. Sample size estimation indicated that a total sample size of 32 was necessary to detect clinically meaningful differences in NRS_pain_ from baseline to week 12. Based on published evidence of comparative studies of resistance exercise and controls on LBP [21], a sample size of 16 per group will yield a power of 80% at an *α* value of 0.05. To account for the anticipated dropout rate of 25%, the enrollment target will be 40.

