### Randomisation and concealment

Following baseline measures, participants will be randomised to either the HBRX or the CON group. The randomisation will be performed by a clinical coordinator not involved in the study. Permuted block randomization [22] with block sizes of 4 will be made by means of a computer algorithm to ensure balanced group sizes and allocation concealment. Patients will receive an opaque, sealed envelope taken from a sequential order containing information on group allocation.

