### Compliance and attrition

Treatment compliance will be assessed by recording the number of completed HBRX training sessions. Participants will be asked to keep an exercise log indicating the exercises performed and RISE and RPE scores for each exercise. Compliance will be defined as completing 85% of all sessions [20]. Members of the study team will be monitoring the exercise performance on a weekly basis. If participants did not remain compliant, their data will not be included in the final analysis. When applicable, participants will be asked for their reasons for poor compliance or dropout. We will collect, assess, and report any spontaneously described adverse events from participants using RedCap data forms. Any unintended or unanticipated adverse events will be reviewed by study physicians for potential medical management. All symptoms will be prospectively followed by phone or in-person until resolution.

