### Statistical analysis

Statistical analysis will be performed using the Statistical package for the Social Sciences (SPSS v. 24, IBM Corporation, Armonk, NY, USA). An *α* level will be established at 0.05 a priori for all statistical tests. Data will first be examined for normal distribution using the Kolmogorov-Smirnov test, and skewness and kurtosis parameters. Descriptive statistics will be performed to characterize the participants. Means, standard deviation, and frequencies will be obtained for both study groups. The chi-square test for frequency distributions will be used for demographics, and amputation type. Continuous data that are not normally distributed will be transformed prior to analysis.

The main analysis type that will be used to test the hypotheses of aims 1 and 2 will be a mixed-model, repeated measures approach. These analyses will examine the main effects of the exercise treatment on the study outcomes. The independent variables will include study group (HBRX or CON) and time point (baseline, week 12). Dependent variables will include LBP severity, medication use, perceived impact of LBP on QOL (NRS_pain_, medication number, SF-36, ODI, RMDQ) and biomechanical measures (walking velocity, temporal spatial parameters, GRF, key joint angles). Mixed models are the preferred approach to analyze data with repeated measures; these models account for correlation among repeated measurements, flexible time effects, and handle missing data. To test the hypothesis of aim 3, regression analyses will be used to identify significant contributors to the change in pain over 12 weeks. A hierarchical approach will be used to find the model of best fit. Independent variables that will be entered into the models will include changes in lumbar muscle strength, ultrasound measure of lumbar extensor cross-sectional area, and change scores in SF-36, ODI, and RMDQ. In addition to age, sex, and K-classification, models will be adjusted for other participant characteristics if differences are found from baseline to week 12 (Tampa Scale of Kinesiophobia and Pain Catastrophizing Scale scores, daily step number). Subjects who dropped out or missing participant data will not be included in the final analysis, and intention-to-treat will not be utilized. Due to the relatively small study size, actual treatment effects that would be seen may be washed out during an intention-to-treat analysis.

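### Enrolling 40 covers a 20% loss, not the stated 25%: at 25% dropout 30 participants remain, two short of the 32 the protocol says it needs

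*Protocol article*

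**What the plan says.** The sample size paragraph under Study population gives three figures in succession. The requirement is 32 in total: "Sample size estimation indicated that a total sample size of 32 was necessary to detect clinically meaningful differences". This is then expressed by arm: "a sample size of 16 per group will yield a power of 80" percent, at an alpha of 0.05. Finally comes the allowance for loss: "To account for the anticipated dropout rate of 25%, the enrollment target will be 40".

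Two other sections determine who counts towards the 32. The Statistical analysis section excludes participants who drop out or have missing data from the final analysis and rejects intention-to-treat. The Compliance and attrition section adds a further exclusion, with compliance defined as completing 85% of sessions: "If participants did not remain compliant, their data will not be included in the final analysis".

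**The concern.** An allowance for dropout should leave the required number after the expected loss has occurred. Here the requirement, the expected loss and the target stand next to each other and cannot all be true. A reader is told that 40 protects 80% power against a 25% loss, and on the protocol's own figures it does not.

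What is at stake is the accuracy of the stated power, or of the stated tolerance for dropout, for the primary pain outcome. The trial is small and the analysis is confined to completers, so there is little slack. The discrepancy itself is only two participants.

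**Working it through.** **Inputs from the protocol article**

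- Required evaluable total 32, or 16 per group, for 80% power (Study population).
- Anticipated dropout 25%; enrolment target 40 (Study population).
- Alpha 0.05 (Study population). The Statistical analysis section repeats it: "level will be established at 0.05 a priori for all statistical tests". Sidedness is not stated.
- Two groups with equal allocation; the randomisation is permuted blocks "with block sizes of 4 will be made by means of a computer algorithm to ensure balanced group sizes".
- Dropouts are not analysed (Statistical analysis), so evaluable means completers.
- Effect size and standard deviation: no figure is given. The text says only that the number was "necessary to detect clinically meaningful differences in NRS_pain_ from baseline to week 12".

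**Reproducing the stated target**

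32 × (1 + 0.25) = 40. This form gives the stated figure exactly.

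**The form that preserves 32 after a 25% loss**

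- Total: 32 / (1 − 0.25) = 42.67, so 43.
- Per group: 16 / 0.75 = 21.3, so 22 per group and 44 in total, which is also a whole number of blocks of 4.

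**What 40 delivers**

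- At 25% loss: 40 × 0.75 = 30, or 15 per group; 32 − 30 = 2 short.
- Loss that 40 tolerates while keeping 32: 1 − 32/40 = 20%.
- If each of 40 participants drops out independently with probability 0.25, the chance of at least 32 completers is about 30%.

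**Power at 15 per group**

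Because no effect size is given, it must be back-solved. The assumptions are a two-sample t-test, two-sided alpha of 0.05, and exactly 80% power at 16 per group.

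- Noncentral t: standardised effect d = 1.024; power at 15 per group 77.2%.
- Normal approximation: d = (1.960 + 0.842) × √(2/16) = 0.991; power at 15 per group 77.4%.
- One-sided alpha, noncentral t: d = 0.900; power at 15 per group 77.6%.

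The exact-80% assumption matters. Sample sizes are normally rounded up, and 16 is the smallest whole number per group that reaches 80% for any d from 1.024 to just under 1.060. At d = 1.060, 15 per group would itself give 80%. So, if 16 was rounded up, power at 15 per group lies between 77.2% and just under 80%.

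**The case against.** The strongest objection is one of size. The gap is two evaluable participants and at most about three percentage points of power; no estimand, error rate or participant exposure changes. That stands, and it makes this a minor correction.

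Second, a reader might infer that the trial falls materially short of 80% power. The documents do not support so firm a claim. The source calculation is not shown, there is no effect size or standard deviation, and 16 may have been rounded up. What is certain is that 30 is below 32; the 77% is conditional on stated assumptions.

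Third, a mixed model can use incomplete data, and the Statistical analysis section says as much. That would help if dropouts stayed in the analysis, but the same section takes them out.

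Fourth, it is tempting to say that the compliance exclusions were overlooked and push power well below 77%. The protocol gives no expected rate of non-compliance, and it does not say whether the 25% already includes these exclusions; it handles compliance and attrition under one heading. Any figure for this further loss would be invented. All that can be said is that exclusions beyond the allowance would lower the evaluable number further.

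Finally, that the target came from multiplying by 1.25 is an inference from the exact match. The protocol does not state its method, and the inconsistency does not depend on it.

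**Conclusion.** The sentence is wrong as written. The requirement of 32, the 25% loss and the target of 40 are mutually inconsistent, and nothing elsewhere in the article reconciles them. That conclusion rests on arithmetic and on the stated exclusion of dropouts.

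The consequence is small: 30 evaluable in place of 32, with power of about 77% to just under 80%, given a two-sample t-test, two-sided 0.05 and an effect inferred from the protocol's own 16 per group. Whether the compliance exclusions fall inside the allowance is unclear. Whether those exclusions should be made at all, and whether the analysis should adjust for baseline, are separate questions; neither would correct this figure.

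**What to change.** Keep the target of 40 and restate the sentence in one of two ways:

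- 40 allows for a 20% loss, leaving 32 evaluable and the stated 80% power; or
- at the anticipated 25% loss, 30 are evaluable, with power of about 77% for the same effect.

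In the same place, say whether the allowance includes participants excluded for completing less than 85% of sessions.

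The cost is one sentence and a slightly less favourable stated power or tolerated dropout. No additional participants are needed. Only if the sponsor wishes to keep both the 25% and the 32 would the target have to rise, to 43, or 44 with equal arms.

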### Randomisation and concealment

Following baseline measures, participants will be randomised to either the HBRX or the CON group. The randomisation will be performed by a clinical coordinator not involved in the study. Permuted block randomization [22] with block sizes of 4 will be made by means of a computer algorithm to ensure balanced group sizes and allocation concealment. Patients will receive an opaque, sealed envelope taken from a sequential order containing information on group allocation.

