### Home-based resistance exercise (HBRX) intervention

Participants in the HBRX group will be coached, by a qualified study team member, through six phases of the intervention with 2 weeks per phase. Table 1 summarizes the HBRX intervention. Body weight and elastic exercise bands will be used to provide resistance. The lightest resistance band is 3.7 lbs which is low enough for all qualified participants to perform with. Moreover, modifications to exercises are available to accommodate such things as pain. For all exercises, the amputees will wear their prosthetic. A set of commercial elastic resistive bands (TheraBand® CLX) and a stability trainer (Fig. 3; Performance Health, Akron, OH, USA) will be provided to each participant. The use of elastic bands for resistance training can induce results in neuromuscular adaptations and strength similar to those achieved by weight machines and free-weights [23–26].

**Table 1 Tab1:** Home-based resistance exercise intervention

Exercise	Description	Progression of exercise
Plank	Prone lying static position with participant’s weight resting on their forearms while holding their body in a straight line from head to toe. Hold this position, with good form, for as long as possible	Progress to an unstable surface/instability disk
Seated resisted back extension^a^	While seated, place feet into band loops. Have participants pull end loops of the band and create an “X” in front of them. Fold and raise arms to shoulder height. Participants will bend their trunk forward at the waist and return to a “straight back” seated position	Progress to an increased resistance band level
Trunk rotary stabilization^a^	With resistance band anchored at chest level, create tension with band. While standing in line with the band, fully extend arm out to participant’s side at about 30°. Use other hand to push the band forward while maintaining stability in participant’s core. Hold this position for 2–3 s and return to starting position to repeat	Progress to an increased resistance band level
Leg extensions^a^	While standing, place feet into band loops with one seal between them. With feet hip width apart, participants will center their balance onto one leg. Keeping one leg straight, slowly raise and kick backwards without touching the ground. Keep back straight and avoid leaning or bending over. Once finished, place foot back into starting position	Progress to an increased resistance band level

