### Trial status

The state of the trial is currently ongoing, and we have not completed patient recruitment at time of submission.

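### One fixed, published block size of 4 leaves an expected third of allocations deducible by anyone who knows the ordered earlier assignments, despite the concealment claimed for it

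*Protocol article*

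**What the plan says.** The section Randomisation and concealment gives one block size, with no variation and no strata: "Permuted block randomization [22] with block sizes of 4 will be made by means of a computer algorithm". It says the scheme is meant "to ensure balanced group sizes and allocation concealment".

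The same section sets three safeguards:
- An outside person randomises: "The randomisation will be performed by a clinical coordinator not involved in the study".
- The allocation is held in sequential, opaque, sealed envelopes.
- Allocation comes late: "Following baseline measures, participants will be randomised to either the HBRX or the CON group".

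The Abstract, the Trial design section and the Discussion describe blinding of the assessor only. In the intervention section, "Participants in the HBRX group will be coached, by a qualified study team member". The wait-list section has controls telephoned monthly while they wait. Outcomes are collected at one university laboratory.

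The Study population section plans equal arms ("a sample size of 16 per group will yield a power of 80" per cent) and states that "the enrollment target will be 40". Under Trial status: "The state of the trial is currently ongoing, and we have not completed patient recruitment at time of submission".

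**The concern.** An envelope hides the next assignment from sight. It does not hide it from someone who can count. With two places per arm in every block of 4, the fourth assignment always follows from the first three, and the third follows whenever the first two are the same. In a trial where the arms are visible to staff, the ordered history may be known to the team, and the article now also makes the block size public.

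Foreknowledge could affect whom staff approach, how they apply the eligibility judgement on symptoms that rule out resistance exercise, or when they book baseline visits. This trial has little to absorb such steering. It is small, the primary outcome is a self-reported change from baseline, and non-compliant participants and dropouts are left out of the final analysis. Placing likely compliers in the exercise arm would therefore carry straight into the result.

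**Working it through.** The document gives no predictability figure, so there is none to reproduce.

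**Inputs**
- Block size 4 (Randomisation and concealment).
- Ratio 1:1, so 2 HBRX and 2 CON per block. This is read from the stated balance and the 16 per group.
- 40 participants (Study population), so 40 / 4 = 10 complete blocks and 20 per arm.
- Observer: assumed to know the block size, where blocks start, and every earlier assignment in order.

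**Certain allocations, fixed blocks of 4**

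A 2:2 block has 6 equally likely orders.
- AABB and BBAA: the last 2 places are determined.
- The other 4 orders: only the last place is determined.
- Expected certain places per block = (2 × 2 + 4 × 1) / 6 = 8/6 = 1.333.
- Share = 1.333 / 4 = 33.3%.
- Over 10 blocks: 13.3 expected, minimum 10 × 1 = 10, maximum 10 × 2 = 20.

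**Best guess, fixed blocks of 4**

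The chance of a correct guess by position is 1/2, 2/3, 2/3 and 1. For the third place, the first two match with probability 1/3 (guess certain) and differ with probability 2/3 (guess right half the time): 1/3 + 2/3 × 1/2 = 2/3. The sum is 17/6 = 2.833, and 2.833 / 4 = 70.8%, against 50% with no such knowledge.

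**Varied blocks, same observer**

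The comparison is fair only if the observer is equally well informed. Here the observer knows the set of sizes and the full history, but not the order of the sizes. Results from 4,000 simulated lists of 40:

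| Scheme | Certain | Best guess correct |
|---|---|---|
| Fixed 4 | 33.3% | 70.8% |
| 4 and 6 at random | 5.6% | 68.9% |
| 4, 6 and 8 at random | about 2% | 67.6% |

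In numbers of participants, 5.6% of 40 is about 2 and 2% of 40 is about 1, against 13.

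**A weaker observer, for scale**

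Someone who tracks only the running difference between arms, without knowing block boundaries, is certain for 8.3% of allocations under fixed blocks of 4 (1/3 per block, divided by 4). The figure is 1.0% under 4 and 6, and 0.1% under 4, 6 and 8.

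**Cost in balance**

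All block sizes and the total of 40 are even, so if the change starts at a block boundary, an unfinished last block has an even number of places used. For a block of 6, the largest difference after 2 or 4 places is 2. For a block of 8, it is 4 after 4 places. The final difference between arms is therefore at most 2 (4 and 6) or 4 (4, 6 and 8).

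**The case against.** A fixed block of 4 with an independent coordinator and sequential opaque envelopes is common in small trials, and nothing here is contradicted or miscalculated. Four points against the concern deserve weight.

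1. **Who knows what.** A reader might infer that the people who recruit also coach and so hold the ordered history. The article does not say this. It names a study team member as coach, lists recruitment sources and gives randomisation to an outsider, but it never says who enrols. This objection stands, and the point has to be conditional.
2. **Timing.** The envelope is opened only after baseline testing, which runs over two visits and includes a week of step monitoring. To use a known slot, staff would have to foresee the order in which people finish baseline. This reduces the practical risk. It does not remove it, because visit timing can be influenced and a determined place is still determined.
3. **Harm.** A reader might infer that selection bias has occurred, or that the assessor is unblinded. The document supports neither. No bias is shown, and its size cannot be computed. The assessor would have to learn other participants' assignments, and the primary outcome is in any case rated by participants who know their own arm.
4. **Size of the gain.** A reader might infer that varied blocks cut certain predictions from 33% to about 1% or less. That pairs a fully informed observer with a weaker one. Like for like, the fall is from 33.3% to about 6% or 2%, or from 8.3% to 1.0% or 0.1%. Best-guess accuracy hardly changes.

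The first point makes the concern conditional, and the others limit its weight. None restores the claim that the block scheme ensures concealment.

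**Conclusion.** The point holds as a cheap improvement, not as a flaw that undermines the trial. The article fixes one block size and credits the scheme with concealment that a constant, disclosed size cannot ensure when only the assessor is blinded. For an observer with the block size and the ordered history, the 33.3% and 70.8% are exact expectations; the realised share of certain allocations lies between 25% (10 of 40) and 50% (20 of 40).

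The conclusion rests on two assumptions: that someone who can influence enrolment or booking knows the earlier assignments in order, and that the full protocol, which is not shown, uses the same single size and no strata.

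**What to change.** Have the outside coordinator generate the unused part of the list with randomly varied block sizes, for example 4 and 6, or 4, 6 and 8, starting at the end of a completed block. Withhold the sizes from the study team and report them once recruitment has closed.

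The costs are modest:
- A final difference between arms of up to 2 participants (4 and 6) or 4 (4, 6 and 8). The plan already expects 25% dropout, which is 10 of 40, so losses may disturb the balance more.
- An amendment. The Ethical aspects section routes protocol changes through the review board and then to the registry and the sponsor.

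The benefit reaches only participants not yet randomised. The article says recruitment was open at submission but not how much of the list remained. If recruitment has since closed, the remaining step is to report the fixed block size and who had access to past assignments as a limitation.
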